#### Follow-up

2.3.3

After discharge from the hospital, an early contrast-MRI is organised to assess the ablation of the target area, and to rule out significant damage to structures adjacent to the prostate. Outpatient visits will occur at 6 weeks, 3, 6, 9 and 12 months. At each, adverse events will be ascertained, PROMs used at baseline are filled and serum PSA level measured. At 6 months, all men undergo a mpMRI and targeted biopsy of the treated area. The biopsy density is set to at least 1 targeted biopsy per 1–2 ml residual prostate volume. Untreated areas will be sampled only if a new suspicious lesion is detected on the 6 months mpMRI or if there is a suspicious change in another area. This sampling strategy aims to minimise the possibility of biopsy-related adverse events by avoiding further sampling of untreated areas, which in the case of a negative mpMRI and a recent template negative biopsy is unlikely to harbour significant disease. As per standard practice, ‘for cause tests’ are permissible at any time point. For instance, a significant unexplained rise in the PSA may drive additional mpMRI scans and/or additional biopsy.

#### Testing alternative forms of follow-up

2.3.4

Patients will be offered an optional embedded qualitative study. This aims to evaluate patient satisfaction in the use of telephone consultation as well as with electronic tools for filling questionnaires. We aim to collect pilot data on patients' satisfaction, usability and acceptability with the use of these tools offering different strategies at different time-points. Patients in this nested study will have a telephone consultation at 6 weeks and will receive their questionnaires at home by post. At 6 months, patients will have a normal clinic visit, but they will complete the questionnaires using a tablet hand-held computer in the research clinic prior to meeting the clinician. At 9 months, patients will have a telephone consultation and will complete online questionnaires. Finally, following the last clinic visit at 12 months, men in the embedded study will be interviewed using a standardized semi-structured questionnaire. The interviews will last around 30 min, and will be audiotaped and transcribed. Thematic extraction will be used to determine whether these men found the method of data collection acceptable, easy to use and would continue to use it. Direct anonymised quotes will be used to illustrate particular themes which evolve. The purpose of the embedded study will be to determine optimal and cost-effective follow-up methods in future studies.

#### Stopping rules

2.3.5

In case a recto-urethral fistula, assessed clinically or radiologically, occurs in any one patient at any time, the IDMC will review the case and make recommendations to the TSC. Any further treatments will be halted while this occurs. We envisage that the target volume will be reduced to the preceding maximum volume. If a recto-urethral fistula occurs in more than one patient, the IDMC and TSC will evaluate whether it is safe to proceed with the trial.

#### Objectives

2.3.6

The primary objective is to determine the adverse events, genito-urinary and rectal side-effect profile at 12 months after focal IRE.

There are a number of secondary objectives included in the study. First, to collect pilot data on the disease control rates of focal IRE for the treatment of prostate cancer localised in the anterior part of the prostate using post-treatment biopsy. Second, to report the rate of patients achieving a trifecta (pad-free/leak-free urinary continence, erections sufficient for penetrative intercourse, and absence of clinically significant disease in the treatment area). Third, to determine domain-specific genito-urinary, rectal toxicity and health-related quality of life after IRE. Fourth, to obtain pilot data on the utility of mpMRI in the follow-up of focal IRE. Fifth, to explore the utility of using a MR/TRUS fusion device for delivering focal IRE. Finally, in men participating within the embedded qualitative study, we will assess patient usability, acceptability and satisfaction in the use of electronic tools and in telephone consultations.

#### Statistical analysis

2.3.7

##### Sample size calculation

2.3.7.1

As the primary objective of the study is to determine the toxicity profile of focal IRE, the sample size was calculated on the basis of common adverse events, which are urinary incontinence and erectile dysfunction. Further, since the results could be used to progress to a IDEAL stage 2b multi-centre therapeutic confirmatory study with 2–3 years of follow-up, it is essential to have a sample size that gives appropriate precision around these key outcomes. Considering an expected proportion of pad-free/leak-free urinary continence of 95%, and a rate at 10% of erectile dysfunction, the ±95% CI around such proportions with n = 10, n = 20 and n = 25 would be at 13.5%, 9.55% and 8.5% for incontinence, and at for 18.6%, 13.2% and 11.8% for erectile dysfunction, respectively. We have therefore chosen to set the sample size at n = 20, as there is significant increased precision from n = 10 (Δ = 3.95% and 5.4%), but little improvement is achieved if more patients are included (Δ = 1.05 and 1.4%).

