**Methods:**

This is a single centre prospective development (stage 2a) study following the IDEAL recommendations for evaluating new surgical procedures. Twenty men who have MRI-visible disease localised in the anterior part of the prostate will be recruited. The sample size permits a precision estimate around key functional outcomes. Inclusion criteria include PSA ≤ 15 ng/ml, Gleason score ≤ 4 + 3, stage T2N0M0 and absence of clinically significant disease outside the treatment area. Treatment delivery will be changed in an adaptive iterative manner so as to allow optimisation of the IRE protocol. After focal IRE, men will be followed during 12 months using validated patient reported outcome measures (IPSS, IIEF-15, UCLA-EPIC, EQ-5D, FACT-P, MAX-PC). Early disease control will be evaluated by mpMRI and targeted transperineal biopsy of the treated area at 6 months.

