##### Primary outcome

2.3.7.2

Primary outcome will be measured by PROMs evaluating sexual, urinary and rectal toxicity. Sexual outcome will be estimated by the rate of men with erectile dysfunction, defined by an inability to have erections sufficient for penetrative intercourse, as measured by the IIEF-15 questionnaire. Primary and secondary outcomes will be reported along with 95% confidence intervals.

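### The ±9.55% and ±13.2% that justify n = 20 are Wald half-widths at expected counts of 1 and 2 in 20, and they overstate the precision this sample gives

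*Protocol article*

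**What the plan says.** Section 2.3.7.1 (Sample size calculation) rests the sample size on precision alone. It assumes an "expected proportion of pad-free/leak-free urinary continence of 95" per cent and "a rate at 10% of erectile dysfunction", and reports "the ±95% CI around such proportions with n = 10, n = 20 and n = 25" as "13.5%, 9.55% and 8.5% for incontinence, and at for 18.6%, 13.2% and 11.8% for erectile dysfunction". It picks n = 20 because the half-widths shrink by 3.95 and 5.4 points from n = 10 to n = 20, but by only 1.05 and 1.4 points from n = 20 to n = 25. It calls appropriate precision essential because the results could be used to move to a stage 2b study.

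The Abstract repeats the rationale: "The sample size permits a precision estimate around key functional outcomes". Section 2.3.7.2 (Primary outcome) adds: "Primary and secondary outcomes will be reported along with 95% confidence intervals". Neither section names an interval method.

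**The concern.** A symmetric ± figure is a fair summary of a binomial interval only when both the number with the event and the number without it are reasonably large. Here the expected proportions lie close to 100% and 0%, and the sample is small. Adding and subtracting the printed figures gives limits that a proportion cannot take.

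Precision is the only reason given for the sample size, and the primary objective is the side-effect profile. A reader who takes the ± figures at face value will think that 20 men can bound the rates of incontinence and erectile dysfunction more tightly than they can, mainly in the direction of harm. If the planning formula were also used for the reported intervals, the same optimism would pass into the results.

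**Working it through.** **Inputs** (section 2.3.7.1): continence p = 0.95; erectile dysfunction p = 0.10; n = 10, 20, 25; 95% two-sided, z = 1.96. The article labels the first set as incontinence. The Wald half-width is the same for p = 0.95 and p = 0.05.

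**Step 1. Reproduce the stated figures.** Wald half-width = 1.96 × √(p(1 − p)/n). For example, 1.96 × √(0.95 × 0.05/20) = 9.55 points, and 1.96 × √(0.10 × 0.90/20) = 13.15 points.

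| n | Continence, computed (stated) | Erectile dysfunction, computed (stated) |
|---|---|---|
| 10 | 13.51 (13.5) | 18.59 (18.6) |
| 20 | 9.55 (9.55) | 13.15 (13.2) |
| 25 | 8.54 (8.5) | 11.76 (11.8) |

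All six agree apart from rounding. At n = 20 the alternatives do not fit: continuity-corrected Wald gives 12.05 and 15.65, Wilson 11.36 and 13.66, Clopper-Pearson 12.37 and 15.23.

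**Step 2. What the stated figures imply at n = 20.** The expected counts are 20 × 0.05 = 1 man not continent and 20 × 0.10 = 2 men with erectile dysfunction.
- Continence: 95 ± 9.55 = 85.5% to 104.5%.
- Erectile dysfunction: 10 ± 13.15 = about -3% to 23%.

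**Step 3. Intervals that suit these counts.**
- Clopper-Pearson (exact): the lower limit is the 2.5% quantile of Beta(x, n − x + 1); the upper limit is the 97.5% quantile of Beta(x + 1, n − x).
- Wilson: centre (p + z²/2n)/(1 + z²/n); half-width z√(p(1 − p)/n + z²/4n²)/(1 + z²/n).

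| Result | Method | 95% limits | Half the width | Distance to the harm-side limit |
|---|---|---|---|---|
| 19/20 continent | Wald (plan) | 85.5 to 104.5 | 9.55 | 9.55 below |
| | Exact | 75.1 to 99.9 | 12.4 | 19.9 below |
| | Wilson | 76.4 to 99.1 | 11.4 | 18.6 below |
| 2/20 erectile dysfunction | Wald (plan) | about -3 to 23 | 13.2 | 13.2 above |
| | Exact | 1.2 to 31.7 | 15.2 | 21.7 above |
| | Wilson | 2.8 to 30.1 | 13.7 | 20.1 above |

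The like-for-like comparison with a ± figure is half the total width. The last column shows that the interval also shifts towards harm.

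**Step 4. Coverage of a nominal 95% interval at n = 20**, summed over the binomial distribution.

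| True rate | Wald | Wilson | Exact |
|---|---|---|---|
| Continence 0.95 | 63.9% | 92.5% | 98.4% |
| Erectile dysfunction 0.10 | 87.6% | 95.7% | 98.9% |

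The Wald shortfall comes almost wholly from samples with no events, where that interval has zero width. Their probabilities are 0.95^20 = 0.358 and 0.90^20 = 0.122.

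**Step 5. Does the choice of n = 20 survive?** Clopper-Pearson half-widths at the expected proportions for n = 10, 20, 25 (beta quantiles used directly where the expected count is not a whole number) are 19.1, 12.4, 10.8 for continence and 22.1, 15.2, 13.5 for erectile dysfunction. The gain from 10 to 20 is 6.7 and 6.9 points; from 20 to 25 it is 1.6 and 1.7. The ordering that the plan relies on holds.

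**The case against.** The best defence is that nothing was miscalculated, that this is a 20-man development study with no hypothesis test, and that n = 20 remains sensible. All of that stands. For erectile dysfunction the Wilson half-width (13.7) is within about half a point of the stated 13.2, so the difference in width is small there and the error lies mainly in where the interval sits. Clopper-Pearson is conservative at these rates, so it gives the larger contrast. The point does not depend on it, because Wilson puts the limits in nearly the same place.

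Some stronger readings are tempting, but the document does not support them:

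- **That the true precision is 19.9 points, not 9.55.** This sets a symmetric half-width against only the longer arm of an asymmetric interval. Like for like, the figures are 12.4 or 11.4.
- **That the reported intervals will under-cover.** Section 2.3.7.2 names no method, and the article may leave that to an analysis plan not shown. The coverage figures condemn the planning formula. They apply to the results only if that formula is reused.
- **That comparing 10 more men with 5 more men makes the argument for n = 20 misleading.** With equal steps of 10 the Wald half-widths at n = 30 are 7.8 and 10.7. The gain from 20 to 30 is therefore 1.75 and 2.4 points, against 3.95 and 5.4 from 10 to 20. Returns still diminish.
- **That the wider limits change a comparison with radical therapy.** The 10–20% incontinence range appears only as background in the Introduction. The plan sets no threshold or decision against it.

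**Conclusion.** The point holds as a fault of method in section 2.3.7.1, not of arithmetic. The stated precision is too favourable. Half the total width at n = 20 is 12.4 points (Wilson 11.4) rather than 9.55 for continence, and 15.2 (Wilson 13.7) rather than 13.2 for erectile dysfunction. The lower continence limit is about 75–76% rather than 85%, and the upper limit for erectile dysfunction is about 30–32% rather than 23%. Continence is the stronger case.

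This assumes that the trial observes the plan's own expected proportions, with all 20 men contributing to both outcomes. The sentences in the Abstract and section 2.3.7.2 are not wrong in themselves. The sample size of 20 is not called into question.

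**What to change.** Keep n = 20. In section 2.3.7.1, replace the ± figures with limits at the expected counts, by one named method:
- 19/20 continent: 75.1% to 99.9% (exact) or 76.4% to 99.1% (Wilson);
- 2/20 with erectile dysfunction: 1.2% to 31.7% (exact) or 2.8% to 30.1% (Wilson).

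Recast the comparison of n = 10, 20 and 25 with the same method; it still favours 20. Use that method for the 95% intervals promised in section 2.3.7.2, so that the planning formula is not carried into the analysis.

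The cost is a rewritten paragraph and one line on method. No patients are added and nothing in the design changes. The stated precision becomes less favourable.

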##### Primary outcome

2.3.7.2

Primary outcome will be measured by PROMs evaluating sexual, urinary and rectal toxicity. Sexual outcome will be estimated by the rate of men with erectile dysfunction, defined by an inability to have erections sufficient for penetrative intercourse, as measured by the IIEF-15 questionnaire. Primary and secondary outcomes will be reported along with 95% confidence intervals.

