All men with a new diagnosis of prostate cancer are counseled about all standard radical therapeutic options. Those meeting the inclusion criteria for the NEAT trial are offered a patient information sheet, and to attend a screening and consent visit if interested. The consent, medical history, physical examination, and blood tests including a PSA test are collected. At baseline, a number of validated patient reported outcome measures (PROMs) are completed: International Prostate Symptom Score (IPSS) and IPSS Quality of Life (IPSS-QoL), 15-Item International Index of Erectile Function (IIEF-15), UCLA Expanded Prostate Cancer Index Composite (EPIC) urinary and bowel domains, EQ-5D Health related Quality-of-life, Functional Assessment of Cancer Therapy for Prostate (FACT-P) and Memorial Anxiety Scale for Prostate Cancer (MAX-PC) [28], [29], [30]. Patients are also asked whether they want to participate to an optional embedded qualitative study aiming to assess patients' satisfaction with alternative electronic forms of follow-up.

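### The primary erectile outcome is a status with no baseline condition, so dysfunction present before treatment would be counted as toxicity of IRE

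*Protocol article*

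**What the plan says.** All references are to the protocol article.

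- **2.3.6 Objectives:** "The primary objective is to determine the adverse events, genito-urinary and rectal side-effect profile at 12 months after focal IRE". A secondary objective is "to report the rate of patients achieving a trifecta", made up of continence, erections sufficient for penetration, and no clinically significant cancer in the treated area.
- **2.3.7.2 Primary outcome:** "Primary outcome will be measured by PROMs evaluating sexual, urinary and rectal toxicity". The erectile component is then defined: "Sexual outcome will be estimated by the rate of men with erectile dysfunction, defined by an inability to have erections sufficient for penetrative intercourse", measured by the IIEF-15. Neither a denominator nor a time point is given there, and no urinary or rectal definition follows.
- **2.3.7.1 Sample size calculation:** "Considering an expected proportion of pad-free/leak-free urinary continence of 95%, and a rate at 10% of erectile dysfunction". These rates are applied to the full 10, 20 or 25 men, and 20 is chosen.
- **2.3.1 Trial entry:** "At baseline, a number of validated patient reported outcome measures (PROMs) are completed", among them the IIEF-15 and the EPIC urinary and bowel domains. Section 2.3.3 repeats them at every outpatient visit.
- **Table 1:** men aged 40 or over can enter. No criterion concerns erectile function.
- **2.1 Study management:** the trial has a single arm.

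**The concern.** Toxicity is something that treatment causes. A count of men who cannot achieve penetration after treatment mixes those who lost the ability with those who never had it at entry. With no control arm, nothing in the design removes the background rate. If IRE harmed no one and no one recovered, the reported figure would simply equal the prevalence at baseline.

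The stake is how the result is read. The Introduction compares focal therapy (erectile dysfunction in 0 to 46%) with radical therapy (about 40 to 95%), and sections 2.3.7.1 and 3 say that the results could inform a larger trial. A rate driven by who happened to be enrolled could make a well-tolerated treatment look harmful. The precision in 2.3.7.1 would also not apply to new dysfunction, because fewer than 20 men would be at risk of it.

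**Working it through.** **1. Reproduce the plan's precision.** Inputs from 2.3.7.1: p = 0.95 (continence) and p = 0.10 (erectile dysfunction); n = 10, 20, 25. Formula: Wald half-width = 1.96 × √(p(1 − p)/n).

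- Continence: 13.51, 9.55 and 8.54 points. The plan: "would be at 13.5%, 9.55% and 8.5% for incontinence".
- Erectile dysfunction: 18.59, 13.15 and 11.76 points. The plan: "18.6%, 13.2% and 11.8% for erectile dysfunction, respectively".

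The arithmetic agrees to rounding. The 10% is applied to every man, which fits an all-men denominator.

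**2. What the stated rate would report.** Let b be the share of men with dysfunction at entry. The documents do not give b, so 10% to 50% is an assumed range. Assume also that none of these men recover and that 10% of the others lose function (the plan's 10%, used here as a new-onset rate for illustration).

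- Reported rate = b + (1 − b) × 0.10
- Share of counted cases that pre-date treatment = b / reported rate

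**3. Precision for new dysfunction.** Men at risk = 20 × (1 − b). Half-width = 1.96 × √(0.10 × 0.90 / men at risk).

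| b (assumed) | Reported rate | Share already present at entry | Men at risk | Half-width for new dysfunction (points) |
|---|---|---|---|---|
| 0% | 10% | 0% | 20 | 13.2 (as stated) |
| 10% | 0.10 + 0.09 = 19% | 53% | 18 | 13.9 |
| 20% | 0.20 + 0.08 = 28% | 71% | 16 | 14.7 |
| 30% | 0.30 + 0.07 = 37% | 81% | 14 | 15.7 |
| 40% | 0.40 + 0.06 = 46% | 87% | 12 | 17.0 |
| 50% | 0.50 + 0.05 = 55% | 91% | 10 | 18.6 |

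At b = 50% the group at risk is 10 men, the size that 2.3.7.1 set aside in favour of 20 on grounds of precision.

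**4. The trifecta.** Section 2.3.7.3 builds it from the sexual and continence outcomes. A man with dysfunction at entry who does not recover cannot reach it, so its ceiling is 1 − b: 70% at b = 30%, even if treatment does no harm and clears all significant cancer.

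**The case against.** **The text may only be abbreviated.** Section 2.3.7.2 states neither that all men are counted nor when, and the full protocol and analysis plan are not shown. The surrounding language (toxicity, adverse events, side effects after IRE) suggests harm that arises after treatment. Section 3.1 also stresses that the baseline and final questionnaires were completed in the same traditional way, which suggests a comparison with baseline. This stands in part: the all-men denominator and the 12-month time point are readings, supported by the n of 20 and the primary objective, and are not stated in the definition itself. But the article does more than stay silent. It gives a definition, that definition is a status, and no section brings the baseline IIEF-15 into it.

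**The 10% planning rate.** A reader might infer that 10% can only be a rate of new dysfunction. The documents do not support that: no source or denominator is given, and 10% lies within the 0 to 46% quoted for focal therapy, also without a denominator. It could be a prevalence if few men have dysfunction at entry; Table 1 simply does not ensure this.

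**Continence and the trifecta.** A reader might extend the same fault to the primary urinary outcome, but 2.3.7.2 gives no urinary definition to criticise. Nor is an all-men trifecta wrong: 2.3.7.3 calls it a status, and the proportion of men who reach a status is a legitimate descriptive secondary outcome.

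**The loss of precision is modest.** This is right for low to moderate b. By the plan's own method, 18 to 14 men give 13.9 to 15.7 points against 13.2. Exact intervals say much the same: 1.2% to 31.7% for 2 of 20, and 0.2% to 33.9% for 1 of 14.

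**The study is small and descriptive.** It has no hypothesis test and no threshold for erectile dysfunction, and its stopping rule concerns fistula only. Because baseline data are collected, the better rate can still be computed at analysis. This lowers the severity but does not remove the mismatch.

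**Conclusion.** The point holds. As written, the estimator of the primary erectile outcome does not measure the side-effect profile named in the primary objective, because dysfunction present at entry would be counted as an effect of IRE.

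Its size cannot be derived from the documents. The 19% to 55% range rests on an assumed baseline prevalence of 10% to 50%, no recovery, and 10% new loss among the rest; it shows sensitivity and is not a forecast. With no dysfunction at entry the problem disappears. A reader might take the table as evidence that the trial's result will be badly inflated, or that 20 men are too few. Neither follows: the true baseline rate is unknown, and the sample-size arithmetic is correct for the denominator it uses.

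This is a change that should be made, not a flaw that stops the study.

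**What to change.** - **2.3.7.2:** define primary erectile toxicity as loss, at 12 months, of erections sufficient for penetration among men who had them at baseline on the IIEF-15. Report the prevalence of dysfunction in all men at baseline and at 12 months beside it, so that every patient still contributes.
- **2.3.7.1:** state that the 13.2-point half-width applies only if all 20 men are potent at baseline, and that with 18, 16, 14 or 10 such men it is about 13.9, 14.7, 15.7 or 18.6 points. No increase in enrolment is needed; the wider interval can be accepted in a development study.
- **2.3.7.3:** keep the all-men trifecta as a descriptive status and add the trifecta among men potent and continent at baseline.

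**Cost:** wording only, since the questionnaires are already collected at baseline and follow-up. The main erectile estimate will rest on fewer than 20 men if any have dysfunction at entry, with a correspondingly wider interval.
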